## Experts’ team

The content and visual validity of the Educational program will be measured, and the comments received from the panel of experts. The panel of experts will be included three professionals from the cardiovascular disease and two experts from the field of nursing and one expert from the health education.

## Phase II: Implementation of educational intervention

In this step, a randomized controlled clinical trial will design to assess the efficacy of prepared protocol. Participants randomly will allocate into two groups. In one experimental group we will implement our designed protocol, and control group will not receive any intervention, but they follow as same as experimental group.

Participants will be selected based on the inclusion criteria and randomly divided into the intervention and control groups. After completing the written informed consent forms, the individuals will complete the pre-test questionnaires and the intervention group will receive the researcher-made educational package. During this time, the control group will not receive any education, but only the routine nursing care. At the post-test stage, that is one month after the intervention, all participants will be asked to complete the questionnaires and the collected data will be analyzed.

## Study environment and population

The patients hospitalized in the critical care units (CCU) of the hospitals affiliated to Shahrekord University of Medical Sciences will be considered for the intervention.

## Study sample

The target participants will include all patients (and their active family members) admitted to CCUs of hospitals affiliated to Shahrekord University of Medical Sciences. The sample size was calculated as 60 (30 participants in each group) based on the previous studies and with respect to the type I error of 0.05 and the test power of 0.80.

## Sampling method

Random sampling’s method will apply to select the participants.

Participants will be divided into the intervention (receiving the training program) and control (not receiving the training program) groups according to the random number table.

## Inclusion criteria

Definitive diagnosis of the myocardial infarction by a cardiovascular specialist for the first time;Admission to the CCU in hospitals affiliated to Shahrekord University of Medical Sciences;Age range of 45 to 88 years;Possibility of making telephone communication;Ability to speak Farsi without having difficulty in speaking, hearing, and seeing;Access and ability to use the computer in order to read the educational files at home;

## Exclusion criteria

Refusal to continue participating in the study;Patient’s death during the research;Prolonged hospital stay due to the disease complications;

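### The exclusion criteria are events that arise, or most naturally arise, after randomisation, so applying them as written drops randomised patients for outcome-related reasons

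*Protocol article*

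**What the plan says.** The section Exclusion criteria of the Protocol article has three entries and no others: "Refusal to continue participating in the study", and then the patient's "death during the research;Prolonged hospital stay due to the disease complications". No time point or duration is attached to the prolonged stay.

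The section Phase II describes how patients enter: "Participants will be selected based on the inclusion criteria and randomly divided into the intervention and control groups". The next sentence runs: "After completing the written informed consent forms, the individuals will complete the pre-test questionnaires". Only the intervention group then receives the educational package; controls have routine nursing care. For the outcome, the same section states that "one month after the intervention, all participants will be asked to complete the questionnaires". Sampling method adds that patients are split into "groups according to the random number table".

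The section Study sample plans 30 patients per group, and Data analysis names the chi-square test and the independent t test. The article defines no analysis set and does not say what happens to the data of a patient who meets an exclusion criterion.

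**The concern.** An exclusion criterion should define who may enter. A rule triggered by what happens to someone after allocation does something else: it removes people from the group to which chance assigned them.

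Two of the three events, death and a complicated stay, are poor courses of the disease whose impact the Minnesota questionnaire measures. Refusal can plausibly depend on the arm, because only the intervention arm has a workshop of 2–3 hours and weekly calls for a month to withdraw from. If patients are removed for such reasons at different rates in the two arms, the unadjusted t test compares differently selected groups. A difference in quality of life or self-efficacy could then appear, or be hidden, without any effect of the education.

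There is also a practical loss. If the post-test is not sought from a patient because that patient counts as excluded, it cannot be recovered later.

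**Working it through.** **Step 1. When does each item act?**

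- Refusal to continue: presupposes that participation has begun, so it arises after entry.
- Death during the research: after entry, by its own wording.
- Prolonged stay from complications: undated. Phase II places selection on the inclusion criteria directly before randomisation and describes no exclusion step there, and the item is listed with two post-entry events. The natural reading is therefore after randomisation. This is a reading of the text, not a statement in it.

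**Step 2. Do the two sections agree?** Phase II asks all participants for the post-test one month after the intervention. Exclusion criteria takes some of them out. A patient alive with a prolonged stay falls under both rules, and nothing says which one governs.

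**Step 3. The plan's own figure.** The sample size is given as 60 (30 per group) at a "type I error of 0.05 and the test power of 0.80". No effect size, standard deviation (SD) or dropout allowance is given, so 60 cannot be reproduced forwards. Solving backwards, two-sided, by the normal approximation: d = (1.960 + 0.842) × √(2/30) = 0.72 SD; with the t distribution, 0.74 SD.

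**Step 4. Shift in one arm's mean (assumed removals).** Let k of 30 patients be removed from one arm, with scores D points worse than the mean m of the other patients in that arm.

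- Mean of all 30: [(30 − k)·m + k·(m + D)]/30 = m + k·D/30.
- Mean after removal: m.
- Shift: k·D/30.

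| k | D (points) | Shift (points) |
|---|---|---|
| 3 | 20 | 2 |
| 3 | 30 | 3 |
| 6 | 30 | 6 |
| 6 | 40 | 8 |

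The values of k and D are assumptions; none comes from the document. D has no meaning for patients who died. The article calls a change of 5 points or more significant, but that is worded as a change in score and not as a difference between arms, so it serves only as a rough yardstick. The k = 3 rows stay below it.

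If both arms lose patients, the spurious difference is (k₁·D₁ − k₂·D₂)/30. This is zero when removals are equal in number and severity.

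**Step 5. Effect on the t test (simulation).** No true effect, 30 per arm, 40,000 runs per setting, the sickest patients removed, and an assumed correlation of 0.5 to 1.0 between severity and outcome:

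| Removed (arm 1 / arm 2) | Spurious difference (SD) | Type I error |
|---|---|---|
| 0 / 0 | none | 4.7–5.1% |
| 3 / 3 | none | 5.5–8.2% |
| 5 / 2 | 0.08–0.16 | 6.6–13.8% |
| 6 / 0 | 0.17–0.34 | 9.7–27.9% |

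Bias in the mean therefore needs removals that differ between arms. With equal removal the type I error still rises somewhat, because exactly the sickest three are cut from each arm and the remaining spread understates the true uncertainty. That is a feature of this extreme assumption.

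**Step 6. Power (conditional).** If 30 per group gives 80% at d = 0.72, then by the normal approximation 27 per group gives 75.7% and 24 per group 70.7%. This holds only if the 30 contain no allowance for losses, which the article does not say.

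**The case against.** The strongest reply has four parts.

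*Timing.* A reader might infer that all three items can only occur after randomisation. For prolonged stay the article does not establish this. The patients are inpatients in critical care units and the workshop is held on the ward, so a complicated stay could be judged before allocation. The contrary evidence is one condensed sentence in an article. This stands: the point is certain for two items and the likeliest reading for the third.

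*Analysis.* A reader might also infer that the trial will be analysed as a completer comparison. No section says so. An analysis set may be defined in a full protocol or SAP that is not shown, and its absence here is not a defect. Phase II's request to all participants even points towards keeping everyone. This stands too. What remains is the rule that the article does state, and its conflict with Phase II.

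*Relabelling.* A patient who has died has no one-month questionnaire, and one who refuses gives none, whatever the list says. That is correct, and the power loss from those two events would arise anyway. The rewording changes the observed data mainly for prolonged stay. For death and refusal it changes whether they are treated as ineligibility or reported by arm as events in randomised patients.

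*Size.* The larger illustrations assume one-arm removal and big score differences. An argument for unequal removal exists only for refusal; nothing suggests that deaths or complicated stays would differ by arm. This stands, and the figures are illustrations only.

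**Conclusion.** The point holds as a defect in a stated rule. Two of the three exclusion criteria can only arise after entry, and the third most naturally acts after randomisation. Followed literally, the list removes randomised patients for reasons related to outcome and, for refusal, plausibly to arm, and it contradicts the request for a post-test from all participants.

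The size of any bias cannot be known from the document. Under assumed removals from one arm only, a shift of 2 points (k = 3, D = 20) to 6 points (k = 6, D = 30) on the 0–105 Minnesota scale is possible. With equal removals and no true effect there is no bias in the mean. The documents do not support the stronger conclusions that the randomised comparison is certainly lost, that a completer analysis is planned, or that power will fall below 80%.

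**What to change.** 1. Take the three items out of Exclusion criteria and record them by arm as post-randomisation events.
2. Seek the post-test from every surviving, consenting randomised participant, including those with a prolonged stay. This brings the section into line with Phase II.
3. Analyse participants in the group to which they were allocated.
4. Report deaths and refusals by arm, with a sensitivity analysis for missing post-tests. Several methods would serve, and the choice can be left to the trial statistician.
5. If prolonged stay is meant to restrict entry, state that it is assessed before randomisation and how it is defined.

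The cost is a change of wording and slightly more follow-up and analysis work; no extra patients are needed. It should be settled before recruitment, because a post-test that is not collected cannot be recovered.

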## Data collection method

### 1. Minnesota Quality of Life Questionnaire

This questionnaire was designed by Rector in 1984 to determine the impact of treatment on quality of life in patients with heart failure (30). This questionnaire is the most common tool used to assess the patients’ quality of life in research studies (31). The Minnesota Questionnaire assesses the patients’ perception from the heart failure effects on the physical, social, and psychological aspects of their lives. This scale contains 21 items dealing with the physical (N = 13), psychological (N = 4), and socio-economic (N = 4) aspects (32). Each question contains 6 criteria ranging from zero (the best situation) to five (the worst condition). The attainable scores can range from zero to 105; higher total scores indicate greater impact of the disease on the patients’ quality of life (i.e., lower quality of life). A change of 5 scores or more shows a significant improvement in severity of symptoms and quality of life. This questionnaire has had high reliability and validity compared to other similar questionnaires and achieved a Cronbach’s alpha of above 0.9 in all previous studies (33).

### 2. Sherer’s General Self-efficacy Questionnaire

It has 17 items on general self-efficacy and measures the individuals’ beliefs about their own ability to overcome different situations. The questionnaire is designed based on a five-point Likert scale (strongly disagree: 1 score, strongly agree: 5 scores). The maximum and minimum attainable scores in this questionnaire are 85 and 17, respectively. The validity and reliability of the questionnaire have been confirmed by Iranian and international studies. The reliability coefficient of this questionnaire was reported as 76% and 79% by Gutman’s split-half method and by Cronbach’s alph, respectively (34).

## Data analysis

We will apply X2 and independent T test to analysis our data by using SPSS version 21.

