
## Methods/design

Two phases are identified to design this study; the first phase includes designing a curriculum by investigating various studies and the panel of experts’ opinions. This phase will be conducted in the form of multimedia training and telephone contact. Multimedia training (including audio, video, image, and animation) over the patients’ lifestyle, nutrition, and care will be conducted through a one-day workshop in 2–3 hours for patients and one of their active family members. The active family member is defined as the primary caregiver, who spends more time with the patient. The educational course will be conducted at a coordinated date and time in the ward where the patients are hospitalized. The researcher will make telephone calls as the educational intervention and continue the follow-ups once a week for one month. The time of telephone calls will be coordinated with the patients and their companions. The tele-communication contents will include verbal encouragement about health behaviors related to the educational and workshop contents. The research team will finalize the contents based on their priorities. The second phase of the intervention will contain a pre/post-test design along with application of Minnesota quality of life and Scherer general self-efficacy standard questionnaires in the intervention (with training) and control (without training) groups.

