## Research hypotheses

Considering the main study purpose, some hypotheses will be considered according to the opinions provided by a panel of experts in cardiovascular diseases, health education, and nursing. Some hypotheses will be:

After the intervention, quality of life is better in the intervention group compared with the control group.

After the intervention, the general self-efficacy is higher in the intervention group than the control group.

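### Both questionnaires are completed before and after the intervention, but the only test named for them is an independent t test: valid under randomisation, but less efficient than adjusting for the pre-test score

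*Protocol article*

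**What the plan says.** - **Design.** Under Methods/design, the second phase "will contain a pre/post-test design along with application of Minnesota quality of life and Scherer general self-efficacy standard questionnaires", in both the intervention and control groups.
- **Baseline.** Under Phase II, after consent "the individuals will complete the pre-test questionnaires and the intervention group will receive the researcher-made educational package".
- **Follow-up.** The same section has a single later assessment: "At the post-test stage, that is one month after the intervention, all participants will be asked to complete the questionnaires".
- **Hypotheses.** Both are comparisons between groups after the intervention: "After the intervention, quality of life is better in the intervention group compared with the control group" and "After the intervention, the general self-efficacy is higher in the intervention group than the control group".
- **Analysis.** The whole section is: "We will apply X2 and independent T test to analysis our data by using SPSS version 21". No covariate, change score or adjusted model is named.
- **Size and allocation.** Study sample gives 60 participants, 30 per group, for a type I error of 0.05 and power of 0.80. Sampling method allocates by random number table, with no stratification described.

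**The concern.** Every participant supplies a pre-test score on each questionnaire, and that score is usually among the best predictors of the post-test score on the same instrument. An independent t test on post-test scores makes no use of it. An independent t test on change scores uses it, but with a fixed coefficient of one instead of the coefficient that the data support, and this adds noise when the pre-post correlation is low.

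The article names its test, so this is a stated choice and not a detail left to an analysis plan. At stake is precision that costs nothing to obtain. With only 30 per arm, the credibility of the result is also at stake if the groups happen to differ at baseline.

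**Working it through.** **Inputs from the article:** 30 per arm, type I error 0.05, power 0.80.

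**Assumptions:** two-sided testing (sidedness is not stated); equal SD at pre-test and post-test; pre-post correlation *r* between 0.2 and 0.7, because the article gives none. The article also gives no effect size or SD, so its figure of 60 cannot be reproduced. The calculation therefore runs backwards from 30 per arm.

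**Step 1. Difference detectable without adjustment.** With the noncentral t distribution, 58 degrees of freedom and noncentrality d × √(30/2), 80% power requires d = 0.736 SD. The normal approximation gives (1.960 + 0.842) × √(2/30) = 0.723 SD.

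**Step 2. Residual variance under each analysis,** relative to the post-test variance:
- post-test t test: 1
- change-score t test: 2(1 − r)
- ANCOVA: 1 − r² (57 degrees of freedom)

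Because 2(1 − r) − (1 − r²) = (1 − r)², the ANCOVA factor is below the change-score factor for every r below 1. Because 2(1 − r) exceeds 1 when r is below 0.5, a change score is then worse than ignoring the baseline.

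**Step 3. Power at d = 0.736, 30 per arm.** The post-test t test has 0.80 throughout. The last column is 30/(1 − r²), the unadjusted size with the same precision.

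| r | Change-score t test | ANCOVA | Equivalent unadjusted n per arm |
|---|---|---|---|
| 0.2 | 0.60 | 0.82 | 31 |
| 0.3 | 0.66 | 0.84 | 33 |
| 0.4 | 0.72 | 0.86 | 36 |
| 0.5 | 0.80 | 0.90 | 40 |
| 0.6 | 0.88 | 0.94 | 47 |
| 0.7 | 0.95 | 0.98 | 59 |

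As an example, at r = 0.5 the ANCOVA factor is 1 − 0.25 = 0.75, the effective difference is 0.736/√0.75 = 0.849, and power is 0.90.

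**Step 4. Cost of estimating the covariate slope.** The table allows for the lost degree of freedom but not for the average variance inflation from chance imbalance in the covariate. For a normal covariate that is 1 + 1/(2 × 30 − 4) = 57/56, about 2%. It lowers each ANCOVA power above by less than 0.01. Break-even with the post-test t test is at (1 − r²) × 57/56 = 1, so r² = 1/57 and r ≈ 0.13. Below that, ANCOVA loses a trivial amount: about 0.79 against 0.80 at r = 0.

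**Step 5. Chance imbalance.** The standard error of a baseline mean difference is √(2/30) = 0.258 SD. A difference above 0.3 SD in either direction has probability 2 × [1 − Φ(0.3/0.258)] = 0.245, and one of 0.5 SD or more has probability 0.053. In a post-test comparison the expected shift is r times the imbalance. An imbalance of 0.3 SD shifts the estimate by 0.5 × 0.3 = 0.15 SD at r = 0.5. An imbalance of 0.5 SD shifts it by 0.25 SD at r = 0.5 and 0.35 SD at r = 0.7, and the type I error given that imbalance is then about 12.6% and 19.9%. Averaged over all randomisations it remains 5%.

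**The case against.** The planned test is sound as it stands, and four stronger readings that a reader might infer are not supported.

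- **That the t test is invalid or biased.** It is not. Allocation is random, so the unadjusted comparison is unbiased with a 5% type I error overall, and on post-test scores it directly tests the stated hypotheses.
- **That the trial misses its power target.** Nothing shows this. The comparison above fixes the unadjusted test at 80% by construction, so ANCOVA adds power beyond the target.
- **That the baseline is certainly wasted.** The Data analysis section does not say which score is tested. The hypotheses point to post-test scores, but the Minnesota questionnaire is interpreted through a change of 5 points or more. If change scores are meant, the baseline is used, and at r = 0.7 the loss against ANCOVA is small (0.95 against 0.98).
- **That a baseline difference passes in full into the result.** Only r times it does in a post-test comparison. The t test's standard error already contains this variation, so imbalance and lost precision are largely one phenomenon and should not be counted as two separate harms.

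It is also fair that the correlation is an assumption. The pre-test is taken around a coronary care admission for a first infarction, so low values cannot be ruled out, and at r = 0.1 to 0.3 ANCOVA power is only 0.80 to 0.84. Finally, a journal article condenses a longer protocol.

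All of this limits the size and seriousness of the point. It does not remove it: the article does name a test, and on either reading that test is less efficient than baseline adjustment over the range r = 0.2 to 0.7.

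**Conclusion.** The point holds as a recommended improvement to a stated method, not as an error that would spoil the result. For r from 0.2 to 0.7, ANCOVA raises power by 0.02 to 0.18 over a post-test t test (0.82 − 0.80 to 0.98 − 0.80) and by 0.22 down to 0.03 over a change-score t test (0.82 − 0.60 to 0.98 − 0.95). The gain is modest if the correlation is low and substantial if it is 0.5 or more.

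These figures rest on two-sided testing, equal SDs at the two assessments, no loss to follow-up, and a correlation that the documents do not supply. The direction does not depend on the exact correlation, except that below about 0.13 adjustment brings no gain over the post-test comparison and a negligible loss. Naming one model also settles which score is analysed before outcomes are seen.

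**What to change.** In Data analysis, state that the main analysis of each outcome is an ANCOVA of the post-test total score on randomised group, with the pre-test score of the same questionnaire as covariate, and that the adjusted mean difference is reported with its 95% CI. Keep the independent t test as a sensitivity analysis and say which score it uses. Make the change before outcome data are examined, because adjustment adopted after an imbalance has been seen is less credible.

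The cost is one or two sentences. The pre-test scores are already collected, SPSS 21 fits the model, and no further participants or assessments are needed.

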## Outcome measures

Quality of life includes physical, psychological, economic, and social dimensions, which will be measured by the Minnesota Quality of Life Questionnaire.General self-efficacy, which includes the individual’s beliefs about their ability to overcome different situations, will be measured by the Sherer General Self-efficacy Questionnaire.

## Discussion

The present study provides useful data for designing a family-based multimedia educational intervention using the telephone-tracking method (tele-nursing) to improve the quality of life and self-efficacy in patients with myocardial infarction.

Asgari et al. examined the effect of family-based education on laboratory parameters of patients after myocardial infarction and showed that the family-based educational model improved the laboratory parameters of patients with myocardial infarction [2].

Vahedian et al. reported that implementing a family-based empowerment model was practically feasible for patients with myocardial infarction and improved their quality of life [13]. Behzad et al. showed that the telephone follow-up empowerment program was effective in promoting self-efficacy in self-care behaviors among elderly people with hypertension [4]. Diane Inman et al. also investigated the impact of tele-nursing on patients with prostate surgery. Their results showed that 47% of the intervention group members needed less care facilities than the controls [9].

In the present training package, the educational media will be incorporated to enhance education outcomes; so, it can be effective in supporting patients with cardiovascular diseases. It can also reduce their medical and treatment costs. We suppose this program has capacity to integrate into the professionally health care guidelines, so that it can help medical, nurses and health care providers pay attention to the important role of the heart patient health, especially during stay in CCU. The strategies of this program could be important and cost effective, and therefore we hope that the success of such a program is a step forward in improving cardiovascular patient’s health status. Furthermore, the strategy used in this protocol can be applied to provide care and implement tele-nursing in other chronic diseases.
